## Assignment of interventions: randomisation

### Sequence generation: who will generate the sequence {21a}

A statistician at York Trials Unit, who has no involvement with settings or in setting recruitment, will randomise educational settings to either receive II alongside usual care or usual care alone. Once a setting is considered ready to randomise, i.e. baseline data collection is complete, the trial manager or trial coordinator will enter relevant details about that setting for randomisation onto a spreadsheet prepared by the trial statistician. The statistician will then randomise the setting as described in section {21b}.

### Sequence generation: type of randomisation {21b}

Educational settings will be randomised to either receive II alongside usual care or usual care alone, using a 1:1 allocation ratio. Educational settings will be randomised via minimisation to ensure the best possible balance across educational setting characteristics within each group. A dedicated computer programme, MinimPY [23], will be used with the following minimisation factors:Age range of educational setting (primary age only (up to 11 years); non-primary (age 11 +); all age educational settings)Residential status of educational settings (residential; non-residential)Number of children and young people with PMLD (latest available data dichotomised at the median for recruited educational setting in the first batch to be randomised)Local authority region (East Midlands, East of England, London, North East, North West, Scotland or Wales, South East, South West, West Midlands, Yorkshire and Humber)

### Allocation concealment mechanism {22}

Randomisation will take place after eligibility has been confirmed, consent has been obtained, and baseline data collection from an educational professional has been completed. Randomisation and allocation to treatment groups will be conducted by the trial statistician who will have had no prior involvement in the recruitment or set-up of settings.

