#### Secondary outcomes

Secondary outcomes will also be collected at baseline, 32- and 52- weeks post-randomisation. These are outlined below, grouped by respondent.

Parent questionnaires:Quality of Life–Profound Multiple Disabilities (QOL-PMD): measuring quality of life [15]: mean difference in total scores between groups at 32 and 52 weeks adjusting for baselineShort Warwick-Edinburgh Mental Well-being Scale (SWEMWBS): measuring parental wellbeing [16]: mean difference in total scores between groups at 32 and 52 weeks adjusting for baselineMood, Interest and Pleasure Questionnaire—Short Form (MIPQ-S) [17]: mean difference in total scores between groups at 32 and 52 weeks adjusting for baseline

Teacher questionnaires:Modified Routes for Learning [18]: mean difference in total scores between groups at 32 and 52 weeks adjusting for baselineEducation Health and Care Plan (EHCP) Changes: estimated treatment effects at 32- and 52–weeks and overall will be presented as an odds ratioBehaviour Problems Inventory-Short Form (BPI-S) [19]: mean difference in total scores between groups at 32 and 52 weeks adjusting for baseline

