### Participant timeline {18}

Participants will be enrolled in the study and the baseline assessment completed in the autumn term (September to December). The intervention will be delivered during spring and summer terms (January to May). Data will be collected 32 weeks post-randomisation (June–July) and 52 weeks post-randomisation (November–December).

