### Implementation {23}

The allocation sequence will be generated by the trial statistician who is independent of the trial management team and has no contact with participants or educational settings. The trial statistician will notify the trial management team of the randomisation outcome. The trial management team will notify educational settings and parent/carers. Settings allocated to receive II training will receive further communication from the trial team to confirm whether an in-house SaLT is available to receive training or if an external SaLT is required. Trained SaLTs will be responsible for cascading training to school staff and providing support.

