## Assignment of interventions: blinding

### Who will be blinded {24a}

Due to the nature of the intervention, it will not be possible to blind parents/carers or staff within educational settings to allocation. Members of the research team responsible for coding the CCS data will be blinded to allocation. Any instances of unblinding will be recorded using a bespoke form. In such instances, another member of the research team will be responsible for coding wherever possible. The Data Monitoring Committee (DMC) will have access to the unblinded data during the trial.

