## Data collection and management

### Plans for assessment and collection of outcomes {25a}

Data will be collected at baseline, 32- and 52-weeks post-randomisation from both teachers and parents/carers. The full trial timeline with corresponding activities is presented in Fig. 1. Participant specific activities are presented in a SPIRIT table in Fig. 2 [24]. At baseline, parents/carers will complete a questionnaire online or over the phone with a research assistant. The questionnaire includes some demographic questions about the child/young person and the parent/carer as well as the following outcome measures: QoL-PMD [15], SWEMWBS [16], CHU-9D [20], EQ-5D-Y proxy [21], CES [25], bespoke resource use adapted from a previous study [26].

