#### Secondary analyses

A similar approach to the primary analysis will be adopted for the secondary outcomes, adjusting for baseline scores where appropriate.

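### The randomisation trigger is stated in two ways, and one of them lets a parent/carer baseline be given after the family knows the allocation and still serve as a covariate

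*Protocol article*

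**What the plan says.** Two sections of the protocol article give the condition for randomising a setting.

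- Sequence generation {21a}: "Once a setting is considered ready to randomise, i.e. baseline data collection is complete". No respondent is named.
- Allocation concealment mechanism {22}: randomisation follows confirmed eligibility, consent, and the point at which "baseline data collection from an educational professional has been completed". The parent/carer questionnaire is not in this list.

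What happens next is also stated. Under Implementation {23}, "The trial management team will notify educational settings and parent/carers". Under Who will be blinded {24a}, "it will not be possible to blind parents/carers or staff within educational settings to allocation".

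On the parent questionnaire, section {25a} says: "At baseline, parents/carers will complete a questionnaire online or over the phone with a research assistant". It gives no timing relative to randomisation, and the participant timeline {18} gives only the autumn term as the baseline window.

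The parent baselines then enter the analyses. For QOL-PMD, SWEMWBS and MIPQ-S the outcome is the "mean difference in total scores between groups at 32 and 52 weeks adjusting for baseline". The Secondary analyses section adds: "A similar approach to the primary analysis will be adopted for the secondary outcomes, adjusting for baseline scores where appropriate". The health economic section adjusts its regressions for key covariates that include baseline utility, and the parent questionnaire carries the EQ-5D-Y proxy, CHU-9D and Carer Experience Scale.

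**The concern.** Covariate adjustment in a randomised trial is safe because the covariate is fixed before allocation, so any difference in it between arms is chance. A baseline score given after the respondent knows the arm loses that protection. A parent who has just learned that the setting will receive Intensive Interaction training may rate the child or themselves differently from one told that usual care continues. The model would treat that difference as chance imbalance and correct the treatment effect for it.

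The outcomes exposed are subjective reports by unblinded respondents: QOL-PMD, SWEMWBS and MIPQ-S, together with the parent-rated CHU-9D, Carer Experience Scale and EQ-5D-Y proxy where these serve as economic baselines. The article states the randomisation trigger explicitly, and does so twice in different terms, so this is more than detail left to an analysis plan.

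**Working it through.** **Setting the two triggers side by side.**

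1. If {21a} means all baseline data, parent data included, then {22} understates the condition, and staff following {22} could randomise too early.
2. If {22} defines what {21a} means by complete, randomisation need not wait for parents.
3. In neither section, nor in {18}, {23} or {25a}, is the parent baseline explicitly required to precede randomisation or notification.

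**Which outcomes are exposed.**

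- Primary CCS: the baseline is a teacher-recorded video scored by blinded coders. It falls under the educational professional's data that {22} requires first. Not exposed.
- Teacher-reported outcomes (Routes for Learning, EHCP changes, BPI-S): same protection. Not exposed.
- Parent-reported secondary outcomes and parent-rated economic measures: exposed under {22}.

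**Size, by assumption.** The article gives no share of late baselines, no shift and no covariate slope. The adjusted difference is

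(difference in outcome means) − slope × (difference in baseline means).

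If a share f of baselines is late and allocation moves those scores by d SD in one arm relative to the other, the baseline means differ by f × d, and the bias is about −slope × f × d.

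With slope 0.6 and d = 0.2 SD (both assumed), the absolute bias is:

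- f = 10%: 0.6 × 0.10 × 0.2 = 0.012 SD
- f = 30%: 0.6 × 0.30 × 0.2 = 0.036 SD
- f = 100% (a bound, not a realistic case): 0.6 × 1 × 0.2 = 0.12 SD

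Over a wider grid (slope 0.5–0.7, f 10–50%, d 0.1–0.3 SD) the range runs from 0.5 × 0.1 × 0.1 = 0.005 SD to 0.7 × 0.5 × 0.3 = 0.105 SD. The sign follows the direction of the shift, which cannot be known in advance.

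**Scale for comparison.** The planned sample size reproduces. With a difference of 1, SD 2.08, 90% power and 5% two-sided alpha, 90.9 children per arm are needed. The design effect is 1 + (4 − 1) × 0.09 = 1.27, so 90.9 × 1.27 = 115.5 per arm. Dividing by 4 gives 28.9, so 29 settings per arm; 29/0.9 = 32.2, so 33 per arm, or 66 settings and 330 children. The present point does not touch this figure.

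The analysed number is then about 29 × 4 = 116 per arm. Assume the same ICC for a parent-reported outcome and a baseline correlation of 0.6, which multiplies the standard error by √(1 − 0.36) = 0.8. The standard error of the adjusted difference is about √(2 × 1.27/116) × 0.8 = 0.12 SD. A bias of 0.012–0.036 SD is about 10–30% of one standard error.

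**The case against.** The strongest reply is that {22} lists things that must be done and never says that nothing else is needed. Section {21a} describes the operational step at which a setting is called ready and is unrestricted, and both sections hold if parents have also responded. Baseline sits in September to December, and the first randomisation was on 11 December 2023, so the calendar allows parents to come first. This stands as far as it goes. A reader might infer that randomisation waits for the school's data alone, or that late parent baselines are happening. The article supports neither; it only leaves the second possible.

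The size is wholly assumed and, at plausible late shares, well below one standard error on secondary outcomes. That stands too.

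A reader might also infer that the base-case QALY difference is biased. The documents do not establish this. The health economics outcomes section lists an EQ-5D-Y proxy from both parents and teachers, and the analysis section does not name whose rating gives the base-case utilities, although its data-collection sentence points to parent questionnaires. The route exists only where parent-rated baseline utility is used, and an SD figure does not convert directly into QALYs.

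Handling of late-dated covariates can properly sit in the statistical and health economics analysis plans, which are not shown, so its absence from the article is no fault. What does not fall away is that the article states the trigger in two ways, one of which leaves parents out.

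Finally, making every parent response a condition of randomisation would let one family hold up a setting in a term-bound schedule. That is a fair objection to a strict rule, and the fix below allows for it.

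**Conclusion.** The point holds in a limited form. Sections {21a} and {22} give different randomisation triggers. Under {22} a parent/carer baseline may be completed after the family knows its allocation and still be used as a baseline covariate. This could bias the parent-reported secondary outcomes and the economic results that rely on parent-rated baseline utility. It does not reach the primary CCS analysis or the teacher-reported outcomes.

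The likely size is small: about 0.01–0.04 SD if 10–30% of baselines are late, resting on an assumed slope of 0.6 and shift of 0.2 SD, in an unknown direction. Whether any late baselines exist cannot be told from the article. The point merits action because the check is cheap and can still be done before analysis, not because the expected bias is large.

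**What to change.** **Protocol.** Reconcile {21a} and {22} in one rule. For any setting still to be randomised, seek parent/carer baselines before parents are notified, with a fixed cut-off date after which the setting proceeds, so that one non-responder does not delay the rest.

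**Analysis plans (statistical and health economics).**

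1. Compare the date of each parent baseline with the date on which the family was notified. If notification dates were not kept, the setting's randomisation date is a conservative substitute.
2. Do not use values dated after notification as baseline covariates. Treat them as missing and impute from pre-allocation data without regard to arm, for example by the overall mean. Do not add an indicator for lateness to the model, because lateness arises after randomisation and may itself depend on arm.
3. Report the number of late baselines by arm.
4. Because lateness may differ by arm, run a sensitivity analysis, for instance repeating the models with the recorded values and without baseline adjustment.
5. State whose EQ-5D-Y rating supplies the base-case baseline utility.

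**Cost.** A sentence or two in the protocol, a short rule in each analysis plan and one comparison of dates. A few baselines are lost as covariates, with slightly less precision on secondary outcomes. Notification may be briefly delayed in settings not yet randomised. If no late baselines are found, the check confirms that the analyses are clean on this point.

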### Implementation {23}

The allocation sequence will be generated by the trial statistician who is independent of the trial management team and has no contact with participants or educational settings. The trial statistician will notify the trial management team of the randomisation outcome. The trial management team will notify educational settings and parent/carers. Settings allocated to receive II training will receive further communication from the trial team to confirm whether an in-house SaLT is available to receive training or if an external SaLT is required. Trained SaLTs will be responsible for cascading training to school staff and providing support.

## Assignment of interventions: blinding

### Who will be blinded {24a}

Due to the nature of the intervention, it will not be possible to blind parents/carers or staff within educational settings to allocation. Members of the research team responsible for coding the CCS data will be blinded to allocation. Any instances of unblinding will be recorded using a bespoke form. In such instances, another member of the research team will be responsible for coding wherever possible. The Data Monitoring Committee (DMC) will have access to the unblinded data during the trial.

### How will be blinding be achieved {24b}

Participants will be identified using a unique participant ID. Blinded members of the team will not have access to locations where unblinded data is saved. Educational settings will be reminded not to unblind the blinded team members.

Should a team member become unblinded to a settings’ allocation, an alternative team member will be allocated to code the data for that setting.

### Procedure for unblinding if needed {24c}

As only research team members responsible for coding the CCS data will be blinded, there will be no requirement for unblinding.

## Data collection and management

### Plans for assessment and collection of outcomes {25a}

Data will be collected at baseline, 32- and 52-weeks post-randomisation from both teachers and parents/carers. The full trial timeline with corresponding activities is presented in Fig. 1. Participant specific activities are presented in a SPIRIT table in Fig. 2 [24]. At baseline, parents/carers will complete a questionnaire online or over the phone with a research assistant. The questionnaire includes some demographic questions about the child/young person and the parent/carer as well as the following outcome measures: QoL-PMD [15], SWEMWBS [16], CHU-9D [20], EQ-5D-Y proxy [21], CES [25], bespoke resource use adapted from a previous study [26].

**Fig. 1 Fig1:**
[figure not shown]
Participant flow through the study

**Fig. 2 Fig2:**
[figure not shown]
Participant timeline: schedule of enrolment, interventions, and assessments

Similarly, teachers will also complete an online baseline questionnaire, again asking some demographic questions as well as the following outcome measures: Routes for Learning [18], BPI-S [19]. The teacher baseline questionnaire will also ask questions around education plan changes and in-school resource use.

In addition to the questionnaire, teachers will also be asked to record a video of themselves interacting with the child/young person. These videos will be scored using the CCS by trained coders [12, 13]. Three members of the trial team received training directly from the instrument development team at the University of Kansas. This comprised some independent learning using materials provided by the Kansas team as well as in-person training via videoconferencing. This training was then cascaded to an additional member of the team. Inter-rater reliability will be monitored throughout the coding process with at least 10% of videos being coded by two members of the team. Disagreements will be resolved by way of a discussion.

Parent/carers and teachers will complete questionnaires comprising the same outcome measures at 32- and 52- weeks post-randomisation. Teachers will also complete videos at these time points to be scored using the CCS.

Interventionists in school and at home will be given a session record log to record their use of II. This will be returned to the research team at the end of the intervention period and will be used to understand fidelity.

### Plans to promote participant retention and complete follow-up {25b}

To enhance participant retention and encourage the completion of follow-ups, newsletters will be circulated at appropriate intervals and shortly ahead of follow-up windows. Parents/carers will be offered online or over the phone follow-ups to ensure access. Thank-you payments of £15 will be offered to parents/carers upon completion of the final follow-up questionnaire. Similarly, educational settings will be offered thank-you payments of £350. Educational settings allocated to the control group will be eligible to receive the II training and support after the final follow-ups have been completed, which may act as an additional incentive.

Withdrawal can occur at any point during the study at the request of the parents/carers or educational settings. To try and improve some level of retention, withdrawals will be categorised into one of five categories:

Withdrawal from the intervention (individual level)A parent/carer or setting may choose to withdraw a child or young person from receiving the intervention at any time. Data will continue to be collected with continued agreement from the parent/carer and setting.Withdrawal from the intervention (setting level)A setting may choose to withdraw from delivering the intervention at any time. Data will continue to be collected with continued agreement from the parent/carer and setting.Withdrawal from parent/carer data collection (individual level)A parent/carer may choose to withdraw from providing data at any time. Intervention delivery and data collection from the child’s or young person’s educational setting will continue with agreement from the parent/carer and setting.Full withdrawal (individual level)A parent/carer or setting may choose to fully withdraw a child or young person from receiving the intervention and from data collection at any time. Data will be retained in the dataset with continued agreement from the parent and educational setting.Full withdrawal (setting level)A setting may choose to fully withdraw from participating in the trial at any time. No further data will be collected from the setting. Parent/carer data collection will also be stopped as the team rely on the setting for information communication; for example, if a child was to sadly pass away, the team is usually notified by the setting so that parent/carer communication can be stopped. Data will be retained in the dataset with continued agreement from the parent and educational setting.

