### Harms {17}

Given the nature of the intervention being evaluated, no adverse events (AE) or serious adverse events (SAE) that are unexpected and related are anticipated. However, as the intervention sessions will be novel for the children and young people, and they may intrude on some children’s existing routines, this might cause distress for some children/young people with PMLD.

We will take a non-systematic approach to adverse event approaching, rather we will ask SaLTs, interventionists based at the educational settings and parents/carers in both arms of the trial to report if they have a concern about a participating child or young person or they experience an incident, event, negative change (e.g. to their communication or behaviour) or out of character distress that may be related to taking part in the INTERACT trial.

Following consultation with our research advisory group and drawing on the trial team’s clinical knowledge, we will collect data regarding specific adverse events as follows:New or worsening behaviour that challengesExhibited a level of distress that is out of characterReduced levels of communication.Injured at home or at setting.Hospitalised unexpectedly for any reason or had a planned hospital stay unexpectedly lengthened.Negative changes to sleep patternsReduced access to respite due to changes in behaviour.Moved to a different educational setting unexpectedly due to additional needs.New involvement from Child and Adolescent Mental Health Services.Other concerns (please specify)

Participating SaLTs, interventionists and parent/carers will be provided with the list above and asked to report any occurrences by telephone to York Trials Unit using a dedicated trial telephone number. The trial team will then complete an adverse event form and follow up as appropriate.

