#### Adverse events

Adverse events will be summarised descriptively. The frequency of each of the pre-specified adverse events will be reported by trial arm.

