Mean within-trial estimates of costs and utilities will be generated using regression methods, adjusting for key covariates (including baseline utility), and allowing for any correlation between costs and utilities. Missing data patterns will be analysed to guide the multiple imputation methods used to deal with missing data [27]. Analyses will take an intention-to-treat approach, with findings presented in terms of mean costs and effects for both groups, as incremental cost-effectiveness ratios at 12 months. A non-parametric bootstrap re-sampling method will be used to produce confidence intervals around the cost and QALY differences and the ICER. The bootstrapped results will be presented in cost-effectiveness planes and cost-effectiveness acceptability curves [28]. A set of sensitivity analyses will be conducted to explore the robustness of the cost-effectiveness results. The NICE (2013) Guide to the Methods of Technology Appraisal will be followed wherever possible [29], and a pre-specified health economics analysis plan will be agreed with the trial’s independent groups and signed off by the chief investigators.

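### Death is foreseen but is not a named reportable event, so it would reach the by-arm safety summary only through a spontaneous report under a broader item

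*Protocol article*

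**What the plan says.** Four parts of the protocol article bear on this.

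- **Retention {25b}, full withdrawal at setting level.** Parent/carer data collection stops when a setting leaves, because the team relies on the setting for information. The example given is that "if a child was to sadly pass away, the team is usually notified by the setting so that parent/carer communication can be stopped".
- **Harms {17}, general request.** The article states: "We will take a non-systematic approach to adverse event approaching". Speech and language therapists (SaLTs), setting interventionists and parents/carers in both arms are asked to report concerns, incidents, negative changes or "out of character distress that may be related to taking part in the INTERACT trial".
- **Harms {17}, list.** A new paragraph says "we will collect data regarding specific adverse events as follows" and gives ten entries. They include sleep changes, reduced respite and "Hospitalised unexpectedly for any reason or had a planned hospital stay unexpectedly lengthened". The last is "Other concerns (please specify)". Death is not an entry. The list is handed to reporters, who telephone occurrences to the trials unit. Serious adverse events are mentioned, but the article gives no definition of them and no separate route.
- **Adverse events (statistical methods).** Adverse events get a descriptive summary, and "The frequency of each of the pre-specified adverse events will be reported by trial arm".

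**The concern.** The list is both the prompt given to reporters and the basis for the by-arm frequencies. It names events as modest as disturbed sleep but not the most serious one, although the article itself expects that deaths may occur and says settings usually pass the news on. That expectation is attached to stopping contact with the family. Nothing in the article connects it to the safety record.

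The population has complex health needs (Background {9a}), and epilepsy is recorded at baseline (Other collected variables). A by-arm count of deaths is therefore something the Data Monitoring Committee and readers of the final report will expect. If the count depends on unprompted calls filed under a general heading, it may be incomplete, and incomplete to different degrees in the two arms.

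**Working it through.** **1. Where could a death be recorded?**

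| Route | Would it take a death? | Would the count show it as a death? |
|---|---|---|
| Hospitalisation item | Only if there was an unexpected admission or a lengthened stay | No, it counts admissions |
| Injury item | Only if an injury came first | No |
| Other-concerns entry | Yes, if someone telephones it in as a concern | Not from the frequency alone; the free text must be read |
| General descriptive summary | Yes, if it was reported at all | Possibly; the article does not say |
| Participant flow and withdrawal reasons {27a} | Yes, if the reason is known | Possibly; reasons are reported only where available, and death is not among the five withdrawal categories in {25b} |

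A death at home with no admission or injury matches only the open entry. So capture is possible but not assured, and no row for death is guaranteed.

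**2. Is an unrelated death reportable?** The relatedness phrase is in the paragraph before the list. The sentence introducing the list has no such condition, the instruction after it asks for any occurrences, and the hospitalisation item covers any reason. The two paragraphs can be read either way for an event that is not on the list.

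**3. Is ascertainment alike in the two arms?** SaLTs meet intervention settings and parents weekly for four weeks and then monthly {15c}. Control settings receive training and support only after the 52-week follow-up (Comparator {15a}; {34}). Recruitment {20} describes data from interventionists for the intervention arm only. Two of the three groups of reporters named in Harms {17} are therefore mainly an intervention-arm presence during follow-up. In control settings the request may rest largely on parents/carers, who in this case would be bereaved. Informal notification by the setting is open to both arms, but it is lost when a setting fully withdraws.

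**4. How many deaths might there be?** The article gives no mortality rate, so a 52-week risk of 1% to 3% is assumed for scale.

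- Denominator. The planned sample size reproduces: 2 × 2.08² × (1.960 + 1.282)² / 1² = 90.9 per arm. The design effect is 1 + (4 − 1) × 0.09 = 1.27. Then 90.9 × 1.27 / 4 = 28.9, so 29 settings per arm. 29 / 0.9 = 32.2, so 33 per arm, 66 settings, and 66 × 5 = 330 participants.
- Expected deaths: 330 × 0.01 = 3.3 and 330 × 0.03 = 9.9, or about 1.65 to 4.95 per arm.
- Chance of at least one death at 1%, taking deaths as independent: 1 − 0.99^330 = 0.964.
- One unreported death as a share of an arm's expected count: 1 / 1.65 = 61% at a 1% risk, and 1 / 4.95 = 20% at 3%.

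With counts this small, missing a single death in one arm visibly changes the comparison.

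**The case against.** The strongest case against the point has four parts.

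- **The list has a catch-all.** A reader might infer that deaths are excluded from the by-arm table. The documents do not support that. The open entry is itself one of the ten, so its frequency is reported by arm, and adverse events are also to be summarised generally. This stands: capture is uncertain, not ruled out. It does not make deaths identifiable in a count, nor does it prompt anyone to report one.
- **The remark about a child dying is only an example.** It explains why parent contact ends when a setting withdraws and is not the trial's rule for handling deaths. That is fair, and it shows that the team usually hears of them. It also means that recording them would take little extra work.
- **The article condenses a longer protocol.** Serious adverse events may be defined there with a route for deaths. That cannot be excluded. However, the article prints the list and says that this list is given to reporters, so what they are prompted to report is already fixed here.
- **Handling of outcomes after death belongs elsewhere.** From the statement that "Missing data patterns will be analysed to guide the multiple imputation methods used to deal with missing data", a reader might infer that utilities and costs after death will be imputed. No text says so. Both a statistical analysis plan and a health economics analysis plan are promised and neither is shown, so this is not part of the point.

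Nor do the documents restrict the Data Monitoring Committee to listed events. It has access to unblinded data {24a}, and safety recommendations are within its remit {28a}. The gap is in what is reliably collected for it to see.

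**Conclusion.** The point holds as a weakness in safety collection and tabulation. Death is foreseen, is not a named event, and would enter the by-arm summary only by spontaneous report under a broader item that does not identify it. Whether unrelated deaths are reportable is unclear, and the reporting channels are fuller in the intervention arm.

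It cannot simply be left to the analysis plan, because an analysis plan cannot count deaths that the reporting tool did not reliably capture.

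The scale of about 3 to 10 deaths in 330 rests wholly on the assumed 1% to 3% risk. The exclusion of degenerative conditions and dementia would tend to lower the true figure. The conclusion does not depend on the exact rate. The difference in ascertainment between arms is inferred from who is in contact with whom, not shown by data. The sample size, the primary outcome and the primary analysis are untouched.

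**What to change.** 1. In Harms {17}, add death from any cause to the list, with date and reported cause. State that it is reportable in both arms whether or not anyone thinks it related to the trial.
2. Use the notification that settings already usually give as the route. When the team learns of a death and stops contact with the family, it should complete an adverse event form at the same time.
3. Under Adverse events, report deaths by arm as their own row, and pass them to the Data Monitoring Committee as events.
4. Randomisation began in December 2023, so ask settings once whether any participant already randomised has died, so that all recruitment waves are counted alike.

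The cost is one list item, one table row and a short query to settings, made through the amendment procedure in {31}. The handling of outcomes after death can stay with the statistical and health economics analysis plans.
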